## Abstract

**Introduction:**

A key priority for the UK National Health Service and patients is to ensure that medicines are used safely and effectively. However, medication changes are not always optimally communicated and implemented when patients transfer from hospital into community settings. Heart failure is a common reason for admission to hospital. Patients with heart failure have a high burden of morbidity, mortality and complex pharmacotherapeutic regimens. The Improving the Safety and Continuity Of Medicines management at Transitions of care programme comprises a cluster randomised controlled trial which will test the effectiveness of a complex behavioural intervention aimed at improving medications management at the interface between hospitals discharge and community care. We will conduct a rigorous process evaluation to inform interpretation of the trial findings, inform implementation of the intervention on a wider scale and aid dissemination of the intervention.

**Methods and analysis:**

The process evaluation will be conducted in six purposively selected intervention sites (ie, hospital trusts and associated community pharmacies) using a mixed-methods design. Fidelity and barriers/enablers of implementation of the Medicines at Transitions Intervention (MaTI) will be explored using observation, interviews (20 patients, 40 healthcare professionals), surveys and routine trial data collection on adherence to MaTI. A parallel mixed analysis will be applied. Qualitative data will be thematically analysed using Framework analysis and survey data will be analysed descriptively. Data will be synthesised, triangulated and mapped to the Consolidated Framework for Implementation Research where appropriate. The process evaluation commenced on June 2018 and is due to end on February 2021.

**Ethics and dissemination:**

Approved by Research Ethics Committee and the UK Health Research Authority REC: 18/YH/0017/IRAS: 231 431. Findings will be disseminated via academic and policy conferences, peer-reviewed publications and social media.

**Trial registration number:**

ISRCTN66212970.

Strengths and limitations of this studyAn evaluation of a cluster randomised controlled trial of a complex behavioural intervention for a high priority healthcare issue.Views of patients and health professionals working across both primary and secondary care.A key strength is our mixed methods and the flexibility of our approach in light of emerging issues from the study and the shifts in healthcare practice and policy.The process evaluation is limited to six purposively selected intervention sites.

## Introduction

Heart failure presents a major challenge to healthcare systems globally.^1^ In the UK, it is thought to affect the lives of over 920 000 people.^2^ In a study of four million individuals, heart failure cases have been found to increase 12% from 2002 to 2014.^3^ Myocardial infarction has been identified as a risk for heart failure.^4^ Heart failure is treated by a combination of medication, lifestyle changes and interventional surgery depending on the severity of the condition. Typically, the pharmacological treatment pathway involves a combination of medicines that are titrated to the optimal level that patients can tolerate. If not managed well (or if the patient has not been diagnosed and treated in primary care) they may be admitted to hospital for treatment and to be stabilised. Approximately 5% of all emergency hospital admissions are for heart failure.^5^ Ongoing treatment plans following discharge from hospital may not be fully implemented due to failures in communication between healthcare providers or a lack of specialist staff in the community.^6 7^ Patients may not understand their medicines, what they are for and why they need to take them because, for example, medical language may create a gap in patients’ understanding.^8^ Patients may therefore deteriorate, which can result in a readmission to hospital or death.^9^

### The Improving the Safety and Continuity Of Medicines management at Transitions of care study

Improving the Safety and Continuity Of Medicines management at Transitions of care (ISCOMAT) is a 5-year National Institute for Health Research (NIHR)-funded research programme, which aims to optimise the way heart failure patients are supported with their medicines when they move from hospital to home. This may contribute to improving patients’ health through helping them better understand and use their medicines. ISCOMAT also aims to improve the way health professionals work together in order to improve communication and optimise medicines use when patients return home. Similar international studies have examined patient-centred care transitions for patients hospitalised for heart failure and found clinical outcomes did not improve. ISCOMAT is designed for the UK health system and may show improvements in clinical outcomes in this setting.^10^ In earlier work packages, we explored the resilience of the medicines management pathway for heart failure and then used Experienced Based Co-Design to develop the Medicines at Transitions Intervention (MaTI) with patients and professionals.^8 11^ The MaTI was designed to make best use of medicines and reduce harm through: the provision of information to the patient; enhanced communication between hospital and the patient’s community pharmacist; and increased engagement of the community pharmacist post discharge. We have provided limited information about the intervention here to avoid potential contamination of the ongoing trial. A more detailed description of the MaTI intervention will be published alongside feasibility testing. The cluster randomised controlled trial is testing the effectiveness of the MaTI. Patients will be recruited from cardiology wards in 42 acute National Health Service trusts across England, over approximately 12 months. The recruitment target is 50 patients from each cardiology ward (target n=2100 patients in total). Sites are randomised to either treatment as usual or to the MaTI. A site coordinator is responsible for organising the trial and implementation of the MaTI at each site.

### The process evaluation

Process evaluations are increasingly carried out alongside randomised controlled trials.^12 13^ They are particularly well suited to trials of complex interventions in multiple sites where the intervention may be implemented differently throughout sites and help us to understand more about the practical problems encountered and how they were resolved. We will follow the Medical Research Council (MRC) recommendations and guidance on process evaluations.^13^ The process evaluation will examine the effect of organisational context and setting on intervention delivery, and how the intervention is best implemented. There are no predefined methods that a process evaluation must adopt although they typically involve mixed methods.^14 15^ Although the process and outcomes evaluation will be conducted by separate teams, the trial and process evaluation teams will meet regularly to have oversight.

#### Aims and objectives

The aims of the process evaluation are to inform interpretation of the trial findings, inform implementation of the intervention on a wider scale (eg, other long-term conditions) and aid potential future implementation of the intervention.

Our objectives at each of the six process evaluation sites are to:

Determine the degree to which the intervention is delivered (internal fidelity).Explore and explain the relationship between intervention implementation and the trial outcomes.Identify barriers and facilitators for the successful implementation and roll out of the intervention (should the intervention be effective).

## Methods

### Study design

In addition to the aforementioned MRC guidance,^13^ we will draw on other relevant literature,^16 17^ in particular the Consolidated Framework for Implementation Research (CFIR).^18^ The CFIR is a conceptual framework that was developed to guide systematic assessment of multilevel implementation contexts to identify factors that might influence intervention implementation and effectiveness.^19^ The MaTI intervention is implemented at multiple levels at each site including trusts, secondary and primary healthcare professionals and patients. The CFIR framework generates a knowledge base for implementation across multiple settings within five major domains: intervention characteristics, inner setting, outer setting, individual characteristics and implementation process. Domains will be explored and additional relevant theoretical frameworks applied as appropriate. We will also draw on human resource management evaluation, specifically the ability, motivation and opportunity (AMO) model,^20 21^ and capability, opportunity and motivation (COM-B) model.^22^ These models are complementary and highlight how policy interventions that require changes in staff behaviour are shaped by their ability to work in different ways, in terms of skills, their level of motivation and their opportunities to change practice.

The study design is a parallel mixed synthesis study using quantitative and qualitative data from six intervention sites of the total 42 sites in the cluster randomised controlled trial. Methods will involve non-participant observations, semi-structured interviews and surveys. In order to capture data on barriers and facilitators to implementation we will collect data from health professionals working along the patient pathway (from both secondary and primary care), patients and community pharmacists. We will also use fidelity data on adherence to MaTI that is being collected within each intervention site in the trial. We will explore and explain the relationship between intervention implementation and the trial outcomes in the six process evaluation sites through analysing secondary outcome data. These data will indicate whether the intervention improves patient understanding of their medicines and satisfaction with medicines-related care at 2 and 6 weeks postdischarge and twelve months postregistration from the Patient Experience Survey (PES) (a validated item from Coleman *et al*’s transition measure^23^), alongside observations and implementation data collected as part of the process evaluation. Process evaluations need to be flexible in the context of the ongoing trials they are evaluating and we will record and describe adaptations to this protocol when the findings are published.

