### Sampling and recruitment

We aim to purposively sample six intervention sites based on the following criteria:

University and non-university hospitals.Method for transferring medicines discharge information to community pharmacists’ for example, electronic system, post, telephone.Sites located across different geographic areas of England.

Within each of the six selected sites we will recruit patients and staff for interviews and surveys. We will also conduct observations at each of these sites. The sampling approach will be iterative and following sampling of one-to-two pilot sites; consideration of the initial data in relation to fidelity will be made.

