#### Additional data

Where appropriate, we may consider using the additional data (collected for all sites as part of the wider trial) to inform, explain and triangulate findings with the process evaluation. For example, we may decide that we need more structured information on completion of the MaTI checklist to consider alongside our staff interviews and so clarify which steps of the MaTI different staff members carried out.

Additional data sources include:

Site Feasibility Questionnaire (initial questions sent to sites to assess their suitability to take part in the trial covering areas such as clinical pathways, staffing levels/ types of specialist staff, communication with community pharmacy and the number of patients).PES (completed by patients at 2 weeks/6 weeks/12 months postdischarge).MaTI checklist completed in the hospital (monitors adherence to the main components of the intervention).National Heart Failure Audit Data^27^ (reports on the characteristics of patients admitted with acute or subacute heart failure, in-hospital investigations and care, treatment given and the discharge planning and follow-up).Community pharmacy data collection form (describes implementation within community pharmacy).

Analysis will be integrative in order to clarify and explain the predominant systems and their implications; qualitative and quantitative data will be consolidated through a process of ‘parallel mixed analysis’.^28^ This includes an independent analysis of the quantitative and qualitative data to provide an understanding of key phenomena and the two understandings will be integrated using meta-inferences. For example, key findings will be generated iteratively, explicitly supported by quantitative data (such as structured observational and survey data) and substantiated or augmented by thematic qualitative data (such as interview data and field notes) and vice-versa. Survey data will be compared across the six clusters to identify any differences in staff perceptions of the barriers and facilitators to delivery. Analysis will be descriptive.

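### Survey data from six intervention-only sites are said to indicate whether the intervention improves understanding and satisfaction, but they contain no usual-care comparator and no pre-intervention measurement

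*Protocol article*

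**What the plan says.** The Introduction describes a cluster randomised trial in 42 hospital trusts: "Sites are randomised to either treatment as usual or to the MaTI". It gives that trial the task of testing effectiveness.

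The process evaluation is a separate exercise, "using quantitative and qualitative data from six intervention sites of the total 42 sites in the cluster randomised controlled trial". Under Sampling and recruitment the selection is deliberate: "We aim to purposively sample six intervention sites based on the following criteria". The criteria are university status, the method of sending discharge information to pharmacies, and geography.

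On outcomes, the Study design section says that the team will "explore and explain the relationship between intervention implementation and the trial outcomes in the six process evaluation sites through analysing secondary outcome data". The next sentence draws the inference at issue: "These data will indicate whether the intervention improves patient understanding of their medicines and satisfaction with medicines-related care". It gives the timing as "at 2 and 6 weeks postdischarge and twelve months postregistration from the Patient Experience Survey (PES").

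The Additional data section lists the survey again, as "PES (completed by patients at 2 weeks/6 weeks/12 months postdischarge"), among data gathered for all sites in the wider trial. Use of those all-site data in the process evaluation is optional, and its purpose is to inform, explain and triangulate.

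**The concern.** Whether an intervention improves an outcome is a causal question. Answering it needs the outcome under the intervention and some estimate of the outcome without it. The sentence assigns the question to data that appear to contain only the first of these.

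What is at stake is what the process evaluation may conclude. Its first aim is to help interpret the trial's findings. Read literally, the sentence would allow a statement about benefit from a few treated, hand-picked sites to stand beside the randomised estimate. A satisfactory survey level at those sites could be reported as improvement when usual care might have produced the same level.

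**Working it through.** **1. The stated sample size.** The article gives 42 sites with a target of 50 patients each: 42 × 50 = 2100. This reproduces the stated target, and no figure in the article is in dispute.

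**2. What the sentence refers to.** The sentence before it limits the analysis to "the trial outcomes in the six process evaluation sites through analysing secondary outcome data". The natural antecedent of its opening words is therefore the survey data from those six sites.

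**3. How many patients that is, and in which arm.** At target, 6 × 50 = 300 patients, and 300 / 2100 = 14.3% of the trial. All six sites are intervention sites, so the number under usual care is 0.

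**4. Is there a baseline instead?** The survey times are 2 weeks, 6 weeks and 12 months. The two sections differ on whether the last is counted from registration or from discharge, but that does not matter here, because either way it follows the earlier two. The article places the introduction of the toolkit on the ward around discharge, and the adherence checklist is completed in hospital. So the hospital part of the intervention precedes the first survey. Some community pharmacy contact may come later, but that does not make the 2-week survey a measurement before the intervention. No earlier survey is described.

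**5. What can be estimated.** Write the effect as

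 effect = (mean outcome with the intervention) − (mean outcome without it).

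The six sites inform the first term only. The second is absent both as a concurrent control and as a prior measurement. The figures below are assumed, because the article gives no PES results:

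| Good understanding at the six sites | Usual-care level (not observed) | Implied effect |
|---|---|---|
| 70% | 50% | +20 points |
| 70% | 70% | 0 |
| 70% | 90% | −20 points |

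The same six-site result fits benefit, no effect or harm. More patients at those sites would sharpen the 70% but leave the middle column unknown.

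**6. Does another part of the plan supply the missing term?** The Analysis sections describe framework analysis, mapping to an implementation framework, descriptive statistics, comparison of survey responses across the six clusters on staff perceptions, and integration of the two strands. No comparison of PES data between intervention and usual-care sites is described. All-site data are something the team may consider using. The limitations list mentions the restriction to six purposively chosen sites but not the lack of a comparator.

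**The case against.** The strongest reply is that the sentence describes what the PES is for in the trial as a whole. It is a trial secondary outcome, it is listed among data collected for all sites, and the trial includes treatment-as-usual sites. If the words meant the trial-wide survey compared between randomised arms, the sentence would be sound. That reading is possible but strained. The preceding sentence names the six sites, the use of all-site data is optional, and no between-arm comparison appears. If it is what was meant, the sentence still needs rewording to say so.

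A second reply is that the article leaves effectiveness to the trial, has separate teams for the process and outcome evaluations, and makes roll-out conditional on the intervention proving effective. This stands, and it limits the weight of the point. It does not make the sentence correct. Nor is this detail that an article may leave to a fuller document: the article positively states an inference that the data it names cannot deliver. The verb is mild, but the thing said to be indicated is still an effect.

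A reader might go further than the article allows in three ways:

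- **That a six-site effect estimate, or an analysis of change from 2 weeks to 12 months, is planned.** Neither is described. The stated analysis is descriptive and integrative.
- **That the randomised result would be biased or pre-empted.** Nothing in the article touches the trial's own comparison.
- **That a bias of a definite size follows, such as the whole usual-care survey level.** No estimator is proposed, so there is no bias to size. The problem is non-identification.

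**Conclusion.** The point holds as a moderate one. The article attributes to six-site PES data an inference about improvement that those data cannot support, because they have neither a usual-care comparator nor a pre-intervention measurement. At target, about 300 treated patients and no controls lie behind the statement, and the direction of any effect is undetermined by them.

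This rests on reading the sentence together with the one before it, and on the survey times given being the only ones. If a pre-intervention PES exists in a document not shown, the second half of the argument would weaken. The lack of a control group within the six sites would remain.

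The trial's design, sample size and effectiveness analysis are not affected. The correction concerns what the process evaluation may claim.

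**What to change.** Replace the sentence in the Study design section with wording to this effect: the effect of the intervention on PES understanding and satisfaction will be taken only from the randomised comparison of intervention with usual care across all 42 sites; PES data from the six process-evaluation sites will be used descriptively, to set outcome levels beside fidelity and implementation findings, and will not be treated as evidence of improvement.

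Do not try to repair the sentence by comparing each of the six sites with the control-arm mean. A single purposively chosen cluster set against that mean is not a randomised contrast, and the intervention effect cannot be separated from that site's own cluster effect.

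The cost is one sentence of wording. No new data are needed if the PES is collected at usual-care sites. The Additional data section indicates this by listing the PES among data from all sites, and the authors should confirm it, because the same list includes the adherence checklist, which the Analysis section describes as collected from intervention sites.

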### Sampling and recruitment

We aim to purposively sample six intervention sites based on the following criteria:

University and non-university hospitals.Method for transferring medicines discharge information to community pharmacists’ for example, electronic system, post, telephone.Sites located across different geographic areas of England.

Within each of the six selected sites we will recruit patients and staff for interviews and surveys. We will also conduct observations at each of these sites. The sampling approach will be iterative and following sampling of one-to-two pilot sites; consideration of the initial data in relation to fidelity will be made.

#### Patient interviews

Twenty patients in total will be sampled for interviews (three to four patients across each of the six sites). We will adopt a purposive sampling strategy to meet our target characteristics in terms of gender, age, length of diagnosis and fidelity to intervention. After piloting, we may need to modify our approach to enable diversity in relation to our sampling criteria. Patients approached will be those that have participated in the trial and received the MaTI intervention.

#### Observations of intervention wards

We will seek permission to conduct non-participant observations of staff at ward level (two and a half hours per site). Staff members will be provided with information sheets and a script for informing patients of the researchers’ presence. A maximum of two researchers will be present at any one time. Staff will have the opportunity to opt out of the observation. A potential limitation of conducting overt observation is the Hawthorne effect by which individuals being observed may alter their behaviour because they are aware that they are being studied.^24^ We will seek to minimise the impact by informing staff that they are being observed and we wish them to behave as normal.^25^

#### Hospital staff interviews and surveys

Thirty hospital staff across six sites will be interviewed. Staff members will include those involved in delivering MaTI, such as heart failure specialist nurses, ward pharmacists, pharmacy technicians, cardiology ward nurses and site coordinators. We will identify and recruit secondary care staff through a combination of two approaches: (1) we will use information obtained during our ward observations about staff roles in delivering the intervention and approach staff directly and (2) we will also liaise with the appointed site coordinator to identify staff that are directly involved in the delivery of MaTI.

We will recruit hospital staff for surveys, aiming to recruit as many staff as possible involved in delivering MaTI. We will identify hospital staff with assistance from the site coordinators and seek informed consent from all staff.

